##### Active control group

In the active control group, participants will be free to choose a method for relaxation that is subjectively perceived as effective. Participants will be instructed to decide on a strategy and to keep it during the 15-min relaxation phase. Some suggestions will be given to the participants for orientation; these are listening to music, reading, applying breathing exercises, or meditation. Participants will be encouraged to use their own relaxation method in the instructions. The only posed restrictions will be that it is unrelated to physical activity and can be performed in a sitting position. The applied strategies will be assessed via self-report after the relaxation phase.

##### Mannheim Multi Component Stress Test (MMST)

The MMST applies stressors of different modalities (cognitive, acoustic, emotional, motivational) and has been shown to reliably induce a physiological and subjective stress response [30, 35]. The MMST was programmed in the software Presentation (NBS, San Francisco, USA). As a cognitive stressor, mental arithmetics have to be performed under time pressure (PASAT-C [36];) consisting of the addition of two sequentially presented numbers in the range of 0 to 20. Numbers are shown for 250 ms each with a time latency between numbers of 3 s in the first and 2 s in the second half of the task. Answers have to be marked with the mouse on a numerical keypad presented in the lower part of the screen. Participants will continuously receive performance feedback on the total number of correct answers. As an emotional stressor, 44 negative, fear- and disgust-related pictures are presented for 5 s each as background during the PASAT-C. Five negative pictures are always followed by one positive picture for 3 s to avoid habituation. To direct participants’ attention to the pictures, they have to detect pictures presented twice during an initial 1-min phase before the start of the actual PASAT-C. White noise and 60 randomly timed explosion sounds presented over headphones serve as an additional acoustic stressor. During the first minute of the task, the noise volume is kept constant (75 dB), while with the onset of the PASAT-C, the volume starts to continuously rise to a maximum of 93 dB. As an additional acoustic stressor, explosion sounds are given for incorrect answers. Finally, to induce motivational stress, participants will be told that their reimbursement will be reduced if they perform too poorly.

### Criteria for discontinuing or modifying allocated interventions {11b}

There will be no special criteria for discontinuing or modifying the allocated interventions.

### Strategies to improve adherence to interventions {11c}

Face-to-face instructions will be given throughout the laboratory testing session to increase adherence to the intervention protocol. Adherence to the relaxation instructions will be assessed immediately after the intervention with a short questionnaire. Self-reports and physiological data will be acquired throughout the testing session to monitor the participants’ responses to the study protocol.

### Relevant concomitant care permitted or prohibited during the trial {11d}

Trial participation will not require alteration to usual care pathways (including the use of any medication) in either of both trial arms.

#### Provisions for post-trial care {30}

There is no anticipated harm, and there are no provisions for post-trial care. After study participation, participants will receive compensation in the form of 15 Euros monetary reimbursement or 4.5 participant hours as course credit as well as 4 Euros bonus for their performance in the MMST.

### Outcomes {12}

The primary outcomes are self-reported stress and relaxation measured with a visual analog scale (VAS) at pre- and post-baseline (t2); at the start, middle, and end of the stress induction (t3); at pre- and post-relaxation (t4); at pre- and post-recovery (t5); and in the evening of testing (t6). Secondary outcomes are the physiological parameters, namely heart rate and heart rate variability, tonic skin conductance level as well as the number of non-specific skin conductance responses, systolic and diastolic blood pressure and respiratory rate recorded during the four experimental phases at time points t2 to t5 as well as state mood, and state rumination assessed at four time points (at t2 baseline/pre-stress, at t3 post-stress, at t4 post-relaxation, and at t6 in the evening of testing). Finally, post-event processing will be assessed at t5 after relaxation and at t6 in the evening of testing

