### Objectives {7}

Our main objective is to investigate if the VR intervention is non-inferior to an active control group, applying a freely chosen relaxation method, in inducing stress reduction and relaxation indicated by ratings and physiological measures.

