#### Intervention description {11a}

##### Procedure

Study participation will consist of an online pre-intervention and an online post-intervention survey taking approximately 2 h in total and one laboratory testing of approximately 1.5 h. Online surveys were set up in the online survey tool lime survey (LimeSurvey GmbH, Hamburg, Germany). The pre-intervention survey will assess chronic stress (TICS, [22]), depression, anxiety, and stress (DASS, [23]) as well as trait rumination (RSQ, [24–26]). Testing sessions will take place in the laboratories of the Department of Clinical Psychology and Psychotherapy at the University of Siegen. At the beginning of the testing session, participants will give their informed written consent and will fill out questionnaires on a computer for approximately 30 min. These questionnaires assess perceived stress (PSS-10, [27]), self-efficacy (SWE, [28]), and mindful attention and awareness (MAAS, [29]). The testing session will comprise an initial 5-min baseline measurement, a 5.5-min stress induction by the Mannheim Multicomponent Stress Test (MMST, [30]), subsequently a 15-min relaxation phase, and finally a 5-min recovery measurement. During all of these phases, physiological data will be recorded, namely an electrocardiogram (ECG), galvanic skin conductance response (GSR), respiration, and blood pressure (see description on data collection and management, SPIRIT item 18a for more details). Stress and relaxation ratings will be measured with a visual analog scale (VAS) on a Likert scale ranging from 0 (not stressed, not relaxed) to 9 (very stressed, very relaxed) at pre- and post-baseline; at the start, middle, and end of the stress induction; at pre- and post-relaxation; at pre- and post-recovery; and in the evening of testing. Additionally, two questionnaires on state mood (MDBF, [31, 32]) and state rumination (RSQs, adaptation of RSQ for state [24–26]) will be repeatedly administered at post-baseline, post-stress, and post-relaxation as well as in the evening of testing. Post-event processing (PEPR, translated to German, [33]) will be assessed after relaxation and in the evening of testing. Experienced sense of presence in the VR will be assessed directly after relaxation [34]. Figure 1 shows the procedure for the laboratory testing session.

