### Sample size {14}

Apriori power analyses were performed for a non-inferiority trial in Sealed Envelope Ltd. 2012 [37]. To achieve a power of 90% at an alpha level of 0.05 assuming a non-inferiority margin of 25% and 80% success in both groups, the estimated required sample size is 88. Considering potential dropouts, we decided to acquire data from 100 participants

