### Assignment of interventions: blinding

#### Who will be blinded {17a}

Since participants will be blinded until the onset of the relaxation phase, baseline and stress phases will not be influenced by group assignment. Blinding participants for the relaxation phase will not be possible since either the VR or an own relaxation method will be applied. Similarly, blinding is not possible for the experimenters. The data analysis will comprise two separate processing stages: analysis of raw data in Matlab 2020b (The Mathworks Inc., Natick, MA, USA) and statistical tests in SPSS Statistics 27 (Armonk, NY: IBM Corp.). Missing values and outliers will be treated at the first analysis stage. The data analyst will be blinded until the performance of the statistical test at the second analysis stage.

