### Statistical methods

#### Statistical methods for primary and secondary outcomes {20a}

Analysis of acquired raw data will be conducted in Matlab 2020b (the Mathworks Inc., Natick, MA, USA). All physiological data will be visually screened. ECG data will be analyzed with the Pan-Tompkins algorithm for QRS detection [38, 39]. Heart rate will be estimated as the number of beats per minute. Heart rate variability will be estimated using root mean square of successive differences (RMSSD, [40]). The tonic skin conductance level and the number of non-specific phasic skin conductance responses will be estimated using the matlab toolbox Ledalab [41]. Respiratory rate will be estimated per minute using a custom-made matlab script that band pass filters the data to frequencies of 0.05 to 1 Hz before detection of inhalation peaks and exhalation troughs. SPSS Statistics 27 for Windows (Armonk, NY: IBM Corp.) will be used for statistical analyses. To test the effects of time (within-subject factor), group (between-subject factor), and the time by group interaction, repeated measures ANOVAs will be performed. Additional two sample *t* tests will evaluate the group differences at relaxation and post-relaxation.

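### Two ratings are primary at ten times, six of them before the relaxation; no effect or both/either rule decides non-inferiority, and the comparison that bears on the objective is only additional

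*Protocol article*

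**What the plan says.** Outcomes {12} opens: "The primary outcomes are self-reported stress and relaxation measured with a visual analog scale (VAS) at pre- and post-baseline (t2"). The two outcomes are not ranked. The same sentence then lists the other eight times: "at the start, middle, and end of the stress induction (t3); at pre- and post-relaxation (t4); at pre- and post-recovery (t5); and in the evening". The Procedure section describes each rating as a "visual analog scale (VAS) on a Likert scale ranging from 0 (not stressed, not relaxed) to 9 (very stressed, very relaxed").

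Statistical methods {20a} gives the main analysis: "To test the effects of time (within-subject factor), group (between-subject factor), and the time by group interaction, repeated measures ANOVAs will be performed". The next sentence adds two-sample t tests: these "tests will evaluate the group differences at relaxation and post-relaxation". They are labelled additional.

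The aim in Objectives {7} is non-inferiority: "Our main objective is to investigate if the VR intervention is non-inferior to an active control group".

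On blinding, {17a} says: "Since participants will be blinded until the onset of the relaxation phase, baseline and stress phases will not be influenced by group assignment". Section {17b} adds that allocation is revealed immediately before the relaxation phase.

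Sample size {14} is worked out for a success proportion: "To achieve a power of 90% at an alpha level of 0.05", with 80% success in both groups and a 25% margin, 88 participants are needed, raised to 100 for dropout.

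**The concern.** A non-inferiority claim needs one pre-specified, directional comparison per outcome. The article instead gives primary status to every rating time, including those before either group has relaxed, and gives the informative comparison a subordinate label. Three consequences follow.

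- **The group main effect averages over time.** Ratings taken before the relaxation pull it towards zero. In a non-inferiority trial, shrinkage towards no difference works in favour of the claim.
- **The interaction asks a different question.** With ten levels it has 9 numerator degrees of freedom. It asks whether the group profiles differ in any way, not whether VR is worse by less than a margin.
- **Two outcomes without a rule leave the error rate and power open.** If either outcome suffices, the type I error exceeds the nominal level. If both are needed, the joint power is below that of each.

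**Working it through.** **The plan's own figure.** Normal approximation for two proportions:

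n per arm = (z₀.₉₅ + z₀.₉₀)² × [0.8×0.2 + 0.8×0.2] / 0.25² = (1.645 + 1.282)² × 0.32 / 0.0625 = 43.8, so 44 per arm and 88 in total.

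The stated 88 is reproduced with one-sided alpha 0.05; one-sided 0.025 would give 108. The figure applies to a binary success, and the article gives no cut-off that turns a 0-9 rating into one.

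**Count of ratings (Outcomes {12}).**
- Before relaxation: 2 (baseline) + 3 (stress) + 1 (pre-relaxation) = 6.
- After relaxation: 1 (post-relaxation) + 2 (recovery) + 1 (evening) = 4.
- The statement in {17a} covers the baseline and stress phases, so 2 + 3 = 5 of the six. The sixth, pre-relaxation, belongs to t4, and the article does not say whether it is taken before or after allocation is revealed.

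**Dilution of the group main effect.** Assumptions: all ten ratings are ANOVA levels, no group difference at the six earlier ratings, 50 per arm, compound symmetry with correlation ρ, and a post-relaxation difference d in SD units.
- Difference at post-relaxation only: mean difference = d/10 = 0.1d.
- Difference at all four later ratings: mean difference = 4d/10 = 0.4d.
- Standardised effect = mean difference / √[(1 + 9ρ)/10].

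For d = 0.6:

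| Pattern | ρ | Mean difference | Standardised | Power, group effect |
|---|---|---|---|---|
| Post-relaxation only | 0.3 | 0.06 | 0.10 | 8% |
| Post-relaxation only | 0.5 | 0.06 | 0.08 | 7% |
| All four later ratings | 0.3 | 0.24 | 0.39 | 50% |
| All four later ratings | 0.5 | 0.24 | 0.32 | 36% |

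Power is from the noncentral t at two-sided 5%. A direct t test at post-relaxation has 84%.

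**Time-by-group interaction, same settings.** Noncentrality = (50/2) × Σ(δₜ − mean δ)² / (1 − ρ), with 9 and 882 degrees of freedom.
- Post-relaxation only: Σ = 0.324. Noncentrality is 11.6 (ρ = 0.3) or 16.2 (ρ = 0.5), and power 64% or 81%.
- All four later ratings: Σ = 0.864. Noncentrality is 30.9 or 43.2, and power 99% or nearly 100%.

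The interaction is therefore sensitive to a difference. Its F statistic, however, has no sign and no margin.

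**Two outcomes.** Bivariate normal with correlation r between the two test statistics, one-sided 5% and 90% power each:

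| r | Either suffices: type I error | Both needed: joint power |
|---|---|---|
| 0 | 1 − 0.95² = 9.75% | 0.9² = 81% |
| 0.5 | 8.8% | 83% |
| 0.9 | 6.8% | 87% |

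**The case against.** The strongest reply is that the plan already contains the right comparison: the t tests in {20a} include post-relaxation. The interaction, not the group main effect, is the natural term in such a design, and the earlier ratings help to identify it. A condensed article may also leave factor levels and contrasts to an analysis plan that is not shown.

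Much of this stands. The post-relaxation difference will be examined, dilution affects only one of three ANOVA effects, and the ten levels are an inference, because {20a} does not list them. The either-outcome error also comes close to doubling only if the two ratings are nearly uncorrelated, which is unlikely for stress and relaxation rated at the same moments.

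A reader might infer more: that a real VR deficit will be averaged away and non-inferiority wrongly declared. The documents do not support this. It would require that a non-significant group effect be read as non-inferiority, and no section says so. A reader might also infer that the protocol rules out a group effect at all six earlier ratings; it does so for five. Nor can the missing link between the stated power and the ratings be blamed on the ten time points. It comes mainly from sizing the trial on a binary success.

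The reply does not remove the point. The article itself fixes pre-intervention ratings as primary and ranks the relevant test as additional. Choosing the deciding comparison belongs in {12} and {20a}.

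**Conclusion.** The point holds as a defect of specification. The article designates no decisive effect or time point and no both/either rule, and it gives primary status to six ratings per outcome that precede the relaxation. Of the ANOVA effects, the group main effect would carry 0.1 to 0.4 of a post-relaxation difference if all ten ratings enter. The interaction escapes dilution but, being omnibus and non-directional, cannot answer a one-sided margin question. Depending on the unstated rule, either the error is 6.8% to 9.75% instead of 5%, or the joint power is 81% to 87% instead of 90%.

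The 6/4 count and the factors 0.1 and 0.4 are arithmetic. The power figures rest on an assumed d of 0.6, correlations of 0.3 to 0.5 and compound symmetry; the two-outcome figures rest on assumed correlations of 0 to 0.9. The article gives no SD or correlation from which to check these. The change should be made, but the material does not show that the planned analyses would miss a deficit.

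**What to change.** - **{12} and {20a}:** Make the group comparison at post-relaxation the single primary analysis, reported for each outcome as a confidence interval for the group difference and read against a margin. Adjust for ratings taken before allocation is revealed, namely baseline and end of stress. Use the pre-relaxation rating as a covariate only if it precedes the reveal described in {17b}, and state the order.
- **Two outcomes:** Require non-inferiority on both stress and relaxation, which needs no alpha adjustment.
- **{14}:** State the joint power for that rule.
- **Other ratings:** Treat the recovery and evening ratings and the ten-level ANOVA as secondary, and the baseline and stress ratings as a check on the stress induction.

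A planned contrast or the mean of the later ratings would also be defensible; what matters is that one comparison is fixed in advance.

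The cost is wording and a stated power below 90% for the joint claim if each outcome has 90%. No new data are needed. Trial status says that recruitment ended in May 2021, so the rule should be fixed before the unblinded analysis or reported openly as a change. The planned interim analysis at 50 participants uses the same methods; if it has been run, that should be disclosed with the change.

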### Participant timeline {13}

Figure 3 gives a CONSORT flow diagram for the schedule from enrollment to the end of participation

**Fig. 3 Fig3:**
[figure not shown]
CONSORT flow diagram

A schedule of enrollment, interventions, and assessments is given in Table 1.

**Table 1 Tab1:** Schedule of enrollment, interventions, and assessments. *VR* virtual reality

	Enrollment	Allocation	Study period					
			Pre	Intervention				Post
**Time point**	***-t***_***1***_	**0**	***t***_***1***_	***t***_***2***_	***t***_***3***_	***t***_***4***_	***t***_***5***_	***t***_***6***_
**Enrollment**								
**Eligibility screen**	X							
**Informed consent**	X							
**Allocation**		X						
**Interventions**								
***Stress induction***					X			
***VR relaxation***						X		
***Freely chosen relaxation***						X		
**Assessments**								
**Self-report measures**								
*Depression, anxiety, and stress*			X					
*Chronic stress*			X					
*Trait rumination*			X					
*Perceived stress*			X					
*Self-efficacy*			X					
*Mindful attention and awareness*			X					
*State stress*				X	X	X	X	X
*State relaxation*				X	X	X	X	X
*State mood*				X	X	X		X
*State rumination*				X	X	X		X
*Post-event processing*						X		X
*Sense of presence in VR*						X		
**Physiological data**								
*Heart rate*				X	X	X	X	
*Heart rate variability*				X	X	X	X	
*Tonic skin conductance level*				X	X	X	X	
*Phasic skin conductance responses*				X	X	X	X	
*Respiration rate*				X	X	X	X	
*Systolic and diastolic blood pressure*				X	X	X	X	

### Sample size {14}

Apriori power analyses were performed for a non-inferiority trial in Sealed Envelope Ltd. 2012 [37]. To achieve a power of 90% at an alpha level of 0.05 assuming a non-inferiority margin of 25% and 80% success in both groups, the estimated required sample size is 88. Considering potential dropouts, we decided to acquire data from 100 participants

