## **Introduction**

### Background and rationale {6a}

Repeated or chronic stress is considered a major source of disease, in terms of both somatic and mental illnesses [1]. Stress-related mental disorders do not only lead to subjective suffering but are associated with large economic costs due to health care expenditures, absenteeism, and inability to work [2, 3]. The prevention of stress-related diseases by methods of stress reduction and relaxation techniques has thus an increasing societal relevance. Common relaxation practices, like mindfulness-based stress reduction and meditation techniques, achieve small to moderate efficacy rates [4–6]. They require repeated practice and the capacity to retrieve and apply them in situations of high distress.

Emerging computational power and advances in techniques have rendered the use of virtual realities (VRs) accessible and VRs increasingly immersive [7]. A VR is a 3D simulation of a natural environment that participants can explore by looking or even moving around. New VR systems with a high resolution, a broad field of view, head tracking, and stereo sounds achieve a high level of immersion, i.e., they enable natural sensorimotor perceptions in the VR. They thus have the potential to induce a strong feeling of presence and to shield participants’ attention from distraction [8]. VRs are increasingly used in the field of clinical psychology and behavioral medicine [9, 10]. Applications range from exposure therapy in patients with anxiety disorders, to addiction-related interventions to practices for mindfulness [8–12]. Within the VR, participants can find themselves in a safe space wherein they can practice a specific behavior. An advantage is that a multi-sensory VR for stress reduction does not require prior training but directly targets the process level and could train participants’ relaxation ability online.

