### Trial design {8}

In the current non-inferiority trial, a randomized controlled design is applied, wherein participants will be randomly assigned to one of two parallel groups: either the virtual reality intervention (VR) or an active control group. The allocation ratio will be 1:1. To test the effect of stress reduction, stress will be induced before the relaxation phase (see the description of the procedure for more details).

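### The 88 participants and 90% power are calculated for a binary success outcome that the protocol does not define, so neither the stated power nor the 25% margin applies to the 0–9 primary ratings

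*Protocol article*

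**What the plan says.** The Sample size section {14} opens with "To achieve a power of 90% at an alpha level of 0.05" and continues: "assuming a non-inferiority margin of 25% and 80% success in both groups, the estimated required sample size is 88". The total is then raised to 100 for dropouts. Alpha is not described as one-sided or two-sided. Trial design {8} adds: "The allocation ratio will be 1:1".

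Outcomes {12} states: "The primary outcomes are self-reported stress and relaxation measured with a visual analog scale (VAS"), taken repeatedly from baseline to the evening of testing. The Procedure section places both ratings "on a Likert scale ranging from 0 (not stressed, not relaxed) to 9 (very stressed, very relaxed").

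Statistical methods {20a} plans repeated measures ANOVAs for time, group and their interaction, with additional two-sample t tests of the group difference at relaxation and post-relaxation. Objectives {7} makes non-inferiority the main aim.

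The article gives no cut-off on the rating that would count as success, no analysis of proportions, and no margin in rating points or SD units. Methods for additional analyses {20b} speaks of the success of the relaxation method, but only as a general phrase.

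**The concern.** A success percentage with a percentage margin describes a comparison of two proportions. The primary outcomes are ordered ratings compared as means. If the sample size belongs to one kind of outcome and the analysis to another, the 90% describes a test that the article does not set out.

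In a non-inferiority trial the margin decides the conclusion. The only margin printed is 25%, and it cannot be applied to a mean difference on a 0–9 scale without a further definition. A reader of the eventual result could not tell which deficit of the VR against the freely chosen method had been excluded, or how likely the trial was to exclude it.

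**Working it through.** **Inputs from the protocol article**
- Sample size {14}: success 0.80 in each group, margin 0.25, power 0.90, alpha 0.05, required total 88, planned total 100.
- Trial design {8}: 1:1 allocation.
- Procedure: rating from 0 to 9.

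**Assumptions.** The article gives no SD and no margin for the ratings. SDs of 1.5, 2.0 and 2.5 points and a margin of 1 point are used for illustration only. The true difference is taken as zero.

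**Step 1: reproduce the printed figure.** For two proportions with unpooled variance,

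n per group = (z₁₋α + z₀.₉₀)² × [p₁(1 − p₁) + p₂(1 − p₂)] / margin²

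At one-sided 0.05: (1.645 + 1.282)² × (0.16 + 0.16) / 0.25² = 43.85, rounded up to 44 per group, 88 in total. This matches exactly. Achieved power at 44 per group is Φ(0.25 / √(0.32/44) − 1.645) = Φ(2.932 − 1.645) = 90.1%.

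At one-sided 0.025 the same inputs give 53.80, so 54 per group and 108 in total, which does not match. The printed 88 is therefore a binary calculation with a one-sided alpha of 0.05.

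**Step 2: look for the outcome that this calculation needs.** It requires a yes/no success per participant and a test of the risk difference against −25 percentage points. Outcomes {12} has neither, and Statistical methods {20a} has only ANOVAs and t tests on means. Nothing in the article links a rating to success.

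**Step 3: what the same numbers give for a rating.** Take one two-sample t comparison at one-sided 0.05, with power from the non-central t distribution (df = 2n − 2, non-centrality = margin/SD × √(n/2)). The smallest margin that reaches 90% power is:

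| Per group | Margin in SD | Points at SD 1.5 | SD 2.0 | SD 2.5 |
|---|---|---|---|---|
| 44 | 0.63 | 0.9 | 1.3 | 1.6 |
| 50 | 0.59 | 0.9 | 1.2 | 1.5 |

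The normal approximation for 44 per group gives (1.645 + 1.282) × √(2/44) = 0.62 SD, in agreement.

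Power for a 1-point margin with 44 per group:

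| Assumed SD | 1.5 | 2.0 | 2.5 |
|---|---|---|---|
| Power | 93% | 75% | 59% |

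**Step 4: the opposite direction.** If 25% were read as a quarter of the 9-point range, the margin would be 0.25 × 9 = 2.25 points. Power at 44 per group would then exceed 99% at all three SDs. The answer thus runs from well below 90% to well above it, depending on a margin and an SD that the article does not state.

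**The case against.** Several points can be made for the plan. The arithmetic is correct, and a one-sided 5% level returns the printed total exactly. The article refers to a version 1.0 protocol on a preprint server, which is not at hand and might define success. The figures in SD units are not the trial's power either: they assume one comparison on one outcome, whereas the plan has two primary outcomes and leads with a repeated measures ANOVA. All of this stands. It limits the point to a mismatch between endpoint and sample size, but does not remove the mismatch, because outcome, sample size basis and analysis are all stated in this article and do not fit one another.

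A reader might go further in three ways that the documents do not support.

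- **That the trial is underpowered.** Without a margin and SD for the ratings, power is unknown, and steps 3 and 4 show it on both sides of 90%.
- **That the unstated sidedness is a shortfall because one-sided 2.5% would need 108.** The article never adopts that level. The word one-sided is missing, and adding it settles the matter.
- **That the margin exceeds the benefit of relaxation itself.** This would mean turning 55% against 80% success into a shift on a normal scale and comparing it with the Background's remark that common practices "achieve small to moderate efficacy rates". The conversion needs the very success definition that is absent. The remark carries no number and no SD units, and it concerns mindfulness and meditation practices, whereas the comparator here is any self-chosen method, including music or reading.

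**Conclusion.** The concern holds as a mismatch. The 90% power, the 88 participants and the 25% margin belong to a binary success outcome that the article does not define. They do not apply to the two 0–9 ratings named as primary. This is an error in what is stated, not a detail left to an analysis plan: a later plan could add a margin in rating points, but the printed 90% would still describe a different endpoint.

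The match to 88 rests on the article's own inputs and needs no assumption beyond the one-sided level that it implies. The size of the effect on power cannot be fixed. The 0.63 and 0.59 SD margins, and the range of 93% to 59% for a 1-point margin, are illustrations for a single comparison under assumed SDs. The matter should be corrected before any non-inferiority claim is made.

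**What to change.** Restate {14} on the rating scale, giving:
- a margin in points for stress and one for relaxation, at the post-relaxation rating;
- the assumed SD;
- alpha described as one-sided;
- whether one or both outcomes must meet the margin;
- the power that 88 to 100 participants give on those terms.

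The margin and SD should be justified from sources independent of the trial data. Trial status reports that recruitment ended in May 2021, and Interim analyses {21b} plans a look at 50 participants using the main analyses. Values written now could therefore be chosen with results in view, and if they are set after recruitment they should be labelled so.

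If the binary basis is kept instead, define success on the rating and test the risk difference against −25 percentage points, with matching changes to Outcomes {12} and Statistical methods {20a}.

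The first route costs one rewritten paragraph and possibly a less favourable power figure. The second also changes the stated primary outcomes and analysis. In either case the power should be restated rather than more participants enrolled.
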